#### Economic evaluation

Cost-effectiveness analyses will take the perspective of the publicly funded health care system [71]. The time horizon will capture hospital-based costs and clinical events for mothers and neonates from labour onset to a minimum of 3 months postpartum. Resource use will be identified and measured from patient charts and valued using standardised government sources, following recommended methods for costing in the Canadian context [72]. A discount rate of 5% will be applied, and results will be compared to two scenarios implementing alternative discount rates of 3% to facilitate comparisons with other jurisdictions and 0% to explore the effect of discounting [71].

The main analysis will be an ITT analysis including all trial participants. To assess intervention impact, we will model changes in a composite index of major perinatal morbidities and costs in the two study groups between the 1-year baseline period and the 2-year intervention period using adjusted regression coefficients (with 95% confidence intervals) for the interaction between group (intervention or control) and time period (intervention or baseline) [64, 70]. Costs and effects will be modeled jointly using bivariate multilevel linear models that explicitly recognize potential correlations between the bivariate outcomes (major perinatal morbidities and costs) at individual and cluster (hospital) levels [73]. Crude and adjusted statistical models will be also estimated. Crude models will include study group (intervention vs. control), time period (baseline vs. intervention) and the interaction between study groups and time period. Adjusted models will use precisely the same variables for adjustment of confounding, as the main trial. All variable definitions will be identical to those used for the main trial. To address potential heterogeneity in cost-effectiveness, analyses will be repeated for pre-specified subgroups of interest (level of care, prematurity).

For each analysis, the incremental cost-effectiveness ratio (ICER) statistic will be calculated as the ratio of additional costs per reduction in major perinatal morbidities, and estimate its confidence interval using the Bayesian Markov Chain Monte Carlo (MCMC) method [74]. As interpretation of the ICER can be challenging, the Incremental Net monetary Benefit (INB) will be also calculated using a range of reasonable values to represent societal willingness to pay (*ʎ*) [75, 76]. Analyses will be also conducted to explore the implications of stochastic, parameter and structural uncertainty, as well as heterogeneity [77]. We will use the Bayesian MCMC method to ascertain the joint uncertainty of the estimands, incremental costs and effects [78], and cost-effectiveness planes plotting the values of incremental costs and effects stored in the Markov chains to present the joint uncertainty of the estimands [74]. To explore potential heterogeneity we will repeat all analyses over subgroups based on hospital level of care [74]. Results of the uncertainty analyses will be graphically presented in a cost-effectiveness acceptability curve (CEAC) that depicts the uncertainty about the new intervention being cost-effective as a function of societal willingness to pay (*ʎ*) [77–80]. Finally, we will decompose costs into categories reflecting the secondary trial outcomes to identify drivers of change. Cost-effectiveness models will be implemented in MLwiN [81] within a Stata environment [82]. An independent team not involved in the conduct or analysis of the main trial will perform the economic analyses.

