#### Professional training program from the SOGC

The 5-month implementation period will focus on implementing the PRISMA program in each of the 20 hospitals randomized to the intervention group. In each centre receiving the intervention, health professionals in obstetrics (physicians, nurses qualified in obstetrics, and midwives, if available) will be invited to participate in an onsite 1-day training workshop, provided by certified instructors from the Society of Obstetricians and Gynaecologists of Canada (SOGC), on best practices regarding intrapartum management among women with one prior cesarean delivery, as well as on the PRISMA clinical prediction tools. Using SOGC clinical practice guidelines and algorithms, health personnel will be trained on the following topics: prolonged pregnancy, management of the first and the second stages of labor, induction and stimulation of labor, fetal health surveillance, use of the WHO partograph [52], and assisted vaginal delivery. The SOGC training program will also include a workshop on the criteria to be assessed and discussed with the women during the decision-making process, as well as on the clinical use and interpretation of the Grobman prediction tool and of the ultrasound evaluation of the risk of uterine rupture. The training program will also sensitize participants to maternal factors contributing to the choice of the mode of delivery. Finally, in each hospital receiving the intervention, one or two technicians and physicians, with expertise in sonography, will be identified and invited to receive additional 1-day training in sonographic techniques related to the evaluation of the risk of uterine rupture. A half-day of recertification will be scheduled at the beginning of the second year of the intervention period. The entire training program will be overseen by the SOGC, which possesses extensive expertise in the field of professional training [53]. Details of the training program and algorithms will be available after the trial (September 2019) upon request by email to the corresponding author (NC).

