Each 15-s film will be then immediately sent to a centralized platform in Québec in order to allow an external validation of each film in less than 1 h by experienced experts in measurement of the LUS thickness. This continuous training platform will accelerate the learning curve among health professionals in hospitals from the intervention group. The technicians of the centralized platform will capture three total measurements of the thinnest lower segment for each of the abdominal and endovaginal ultrasounds, based on the two 15-s films, and then send the results to the physician of the LUS clinic at the referring hospital. Once the measurements have been taken and the results of the external validation in Québec are available, the physician responsible of the LUS clinic, who has also been trained, will validate the exam and reproduce it immediately, as required. Only the thinnest measurement, from among the six measurements taken via the abdominal and endovaginal ultrasounds, will be used. For each professional, a continuous quality assessment of the measurement, based on objective criteria, will be conducted during the first 30 measurements of the LUS thickness. Additional training could be considered depending on the performance of each professional [28, 50, 51, 57–59].

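### The economic evaluation counts chart-based hospital costs from labour onset, which leaves most components of delivering PRISMA outside the incremental cost

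*Protocol article*

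**What the plan says.** All references are to the protocol article. Under Economic evaluation it states: "Cost-effectiveness analyses will take the perspective of the publicly funded health care system". The same section fixes three features of the cost side:

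- **Horizon and type of cost:** "hospital-based costs and clinical events for mothers and neonates from labour onset to a minimum of 3 months postpartum".
- **Source:** "Resource use will be identified and measured from patient charts and valued using standardised government sources". No second source is named.
- **Periods:** changes in costs and in the morbidity composite are compared "between the 1-year baseline period and the 2-year intervention period using adjusted regression coefficients" for the group-by-period interaction. The 5-month implementation period belongs to neither.

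The incremental cost-effectiveness ratio (ICER) is "the ratio of additional costs per reduction in major perinatal morbidities", and an incremental net monetary benefit (INB) is calculated over a range of willingness-to-pay values. Costs are later broken down by categories that mirror the secondary clinical outcomes. No category for the programme is mentioned.

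The programme itself is described under Intervention group activities. It includes an "onsite 1-day training workshop, provided by certified instructors", extra sonography training and later recertification, a decision aid and a nomogram used during pregnancy, and an LUS clinic. For the scans, "Each 15-s film will be then immediately sent to a centralized platform in Québec". The Control group section says that control hospitals receive nothing from the PRISMA team.

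**The concern.** A payer deciding on PRISMA needs to know what it costs to deliver as well as what it changes in delivery and neonatal care. The stated start point and data source capture the second and miss most components of the first. The costs missed fall on one arm only, so they do not cancel in the comparison.

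The outputs at stake are the incremental cost, the ICER, the INB and the acceptability curve. This bears on a real decision: under Information and consent forms, the programme is to be offered to control hospitals if it proves effective.

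**Working it through.** The article states no programme cost and no ICER, so there is no figure of its own to reproduce. The check has two parts.

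**1. Each programme component against the stated scope**

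| Component (section) | When and where it arises | Inside the scope? |
|---|---|---|
| SOGC workshops and sonography training (Professional training program) | Hospital level, in the implementation period | No: not a chart item, and in neither modelled period |
| Half-day recertification (same section) | Hospital level, start of intervention year 2 | No: not a chart item |
| Decision aid (Decision analysis tool) | 12+0 to 34+6 weeks | No: before labour for almost all women |
| First nomogram assessment (Grobman nomogram) | 12+0 to 34+6 weeks | No: same reason |
| LUS clinic visit and scans (Ultrasound assessment) | 35+0 to 38+6 weeks; women in labour are not eligible | No: the scan always precedes labour onset |
| Central reading of films (same section) | Central platform | No: not a chart item, and tied to a scan before labour |
| Nomogram completed at admission (Grobman nomogram) | Admission for delivery | Broadly yes |
| Changed intrapartum care | Labour and delivery | Yes |

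**2. Effect on the economic results**

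Let c be the omitted programme cost per intervention-arm woman in the intervention period.

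- *Incremental cost.* The interaction is (intervention arm: intervention period − baseline) − (control arm: intervention period − baseline). Only the first of the four terms lacks c, so the estimated incremental cost is too low by c.
- *INB.* INB = λ × effect − incremental cost, so INB is too high by c at every willingness-to-pay value λ.
- *ICER.* The shift is c divided by the absolute risk reduction.

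Inputs from Sample size and power calculation: baseline rate 4.5%, relative reduction 25%.

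- Absolute reduction = 0.045 × 0.25 = 0.01125, or 1.125 percentage points.
- 1 / 0.01125 = 88.9 women per major morbidity averted.
- ICER shift = c / 0.01125 = 88.9 × c.

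The values of c below are assumptions for illustration only.

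| Assumed c per woman | ICER understated by, at the planned effect | At half the planned effect |
|---|---|---|
| $50 | $4,444 | $8,889 |
| $100 | $8,889 | $17,778 |
| $200 | $17,778 | $35,556 |
| $500 | $44,444 | $88,889 |

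Check on totals: 7360 women per year × 2 years ÷ 2 arms = 7360 intervention-arm women, if the arms are equal in size. At c = $100 the omitted cost is $736,000, against 7360 × 0.01125 = 82.8 cases averted. $736,000 / 82.8 = $8,889, as above.

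**The case against.** The strongest reply is that nothing in the article says programme costs are excluded. The section may describe only how per-patient costs are collected. It refers to recommended Canadian costing methods, and a separate economic plan could add an aggregate programme cost from trial accounts. It also plans analyses of parameter and structural uncertainty. Part of this stands: a deliberate decision to leave the programme out cannot be inferred, and a fuller document may deal with it. But the article does more than stay silent. It fixes a start point, a source and two periods that together exclude most components, and this sits badly with its own perspective. The uncertainty analyses name no programme cost.

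A reader might also infer more than the text supports:

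- **That the whole programme is costed as free.** It is not: the admission-time nomogram and intrapartum care lie within the horizon. An LUS visit may also leave a chart entry, since it produces a consultation form and a written consent. It is the labour-onset start that excludes the visit.
- **That the horizon drops fetal deaths before labour, or women with a planned cesarean and no labour.** The section keeps the main trial's variable definitions and includes all participants, so the effect side is intact.
- **That the open-ended follow-up biases the comparison.** Under Data collection, charts are abstracted at least 3 months after delivery and in the same way in both arms. No difference between arms is shown.

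**Conclusion.** The concern holds for most components of the programme, though not for all of them. Followed as written, the analysis understates incremental cost, and overstates INB, by the omitted delivery cost per woman. The direction of these two errors does not depend on the size of the clinical effect.

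The ICER statement does depend on it. It assumes that the programme reduces morbidity and, for about $8,900 per assumed $100, that it achieves the planned 1.125-point reduction. With half that effect the shift doubles.

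The article gives no programme cost and no delivery or neonatal care costs for comparison. Whether the omission would change a cost-effectiveness conclusion therefore cannot be judged, and a claim that the trial would wrongly report PRISMA as cost-effective goes too far. The point concerns the secondary economic analysis and leaves the primary clinical inference untouched.

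**What to change.** In the Economic evaluation section, state that programme delivery costs are taken from programme records and added to the intervention arm's intervention-period costs, spread over the women delivered there. The items are training (including the set-up sessions in the implementation period), recertification, the decision aid and antepartum nomogram use, LUS visits and scans, and central reading. Separate research-only costs, which matters most for the central platform because it also serves as continuous training.

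The labour-onset start can stay for all other care. Moving the whole horizon back to 12 weeks in both arms is not needed. It would mean costing antenatal care for about 22,080 women, when the article describes abstraction of in-hospital data.

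The cost is a short change of wording, a small amount of costing work from programme records, and a less favourable ICER.

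### The costing rules in the economic evaluation (hospital-based costs, from labour onset, from patient charts) leave most of the program's own cost outside the incremental cost

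*Protocol article*

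**What the plan says.** The *Economic evaluation* section of the Protocol article fixes four things about costs.

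- Perspective: "Cost-effectiveness analyses will take the perspective of the publicly funded health care system".
- Scope and window: "The time horizon will capture hospital-based costs and clinical events for mothers and neonates from labour onset to a minimum of 3 months postpartum".
- Source: "Resource use will be identified and measured from patient charts and valued using standardised government sources", with a reference to recommended Canadian costing methods.
- Estimate: the group-by-period interaction for cost, modelled jointly with major perinatal morbidity. The ICER is additional cost per reduction in morbidity, and an incremental net benefit (INB) and an acceptability curve are also planned.

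The same section adds that "we will decompose costs into categories reflecting the secondary trial outcomes to identify drivers of change". It names no other source of cost data and does not mention the cost of delivering the program.

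The intervention sections describe what the program uses: on-site training workshops, "additional 1-day training in sonographic techniques" for selected staff, a half-day recertification, a decision aid, nomogram assessments, and an LUS clinic visit with two ultrasound examinations. For the central reading, "Each 15-s film will be then immediately sent to a centralized platform in Québec". The *Control group* section plans no intervention there.

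**The concern.** A cost-effectiveness ratio for a program needs the cost of the program in its numerator. Here the stated window opens at labour onset and the stated source is the patient chart, while most of what the program consumes is used before labour or at hospital level. These costs arise in one group only and after baseline, so neither randomization nor the difference-in-differences contrast removes the gap.

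What remains in the numerator is mainly the downstream change in delivery and neonatal costs. The ICER, the INB and the acceptability curve would all lean toward the program. That matters because *Information and consent forms* says the program will be offered to control hospitals if it proves effective, and a public payer weighing wider use needs the delivery cost.

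**Working it through.** **Step 1. Set each component against the stated rules.**

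| Component (section of the Protocol article) | When and where it occurs | Inside the window? | In a patient chart? |
|---|---|---|---|
| Workshops and sonography training (*Professional training program from the SOGC*) | Hospital level, in the 5-month implementation period | No woman-level date | No |
| Recertification (same section) | Hospital level, start of intervention year 2 | No woman-level date | No |
| Decision aid (*Decision analysis tool*) | 12 0/7 to 34 6/7 weeks | No | Possibly |
| First nomogram assessment (*Grobman nomogram*) | 12 0/7 to 34 6/7 weeks | No | Possibly |
| Nomogram update (same section) | After 36 6/7 weeks, using findings at admission | Yes, for women admitted in labour | Possibly |
| LUS visit and scans (*Ultrasound assessment*) | 35 0/7 to 38 6/7 weeks; being in labour makes a woman ineligible | No | Probably |
| Central film reading (same section) | Off site, on the antenatal scan | No | Probably not |

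The barriers differ. For the antenatal contacts it is the start of the window. For training and recertification it is the source. For central reading it is the window and probably the source as well. The implementation period also lies between the two data-collection periods (April 2016 to March 2017, and September 2017 to August 2019), so the initial training cost falls in neither.

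**Step 2. Direction.** Let c be the omitted program cost per intervention-arm woman in the intervention period, counting only what the public payer would bear. The corresponding omission is zero in the control group and at baseline. The group-by-period cost difference is therefore too low by c.

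**Step 3. Size per dollar.** The plan gives no ICER or cost to reproduce. The inputs come from *Sample size and power calculation*: baseline rate 4.5%, relative reduction 25%, 7,360 women per year.

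- Rate under the program: 0.045 × 0.75 = 0.03375.
- Absolute reduction: 0.045 − 0.03375 = 0.01125.
- ICER shift: c / 0.01125 = 88.9 × c.
- INB = λ × (effect) − (cost difference), so the INB is overstated by c at every willingness-to-pay value λ.
- Intervention-arm women over 2 years, if the groups are of equal size: 7,360 × 2 / 2 = 7,360. Events averted: 7,360 × 0.01125 = 82.8.

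**Step 4. Illustration.** The values of c are assumptions.

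| Assumed c per woman | ICER understated by, per event averted |
|---|---|
| $50 | 50 / 0.01125 = $4,444 |
| $100 | 100 / 0.01125 = $8,889 |
| $300 | 300 / 0.01125 = $26,667 |

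The multiplier depends on the effect achieved. With a 10% relative reduction it is 1 / (0.045 × 0.10) = 222.

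**The case against.** The strongest reply is that the article is a condensed account. It nowhere says that charts are the sole source or that program costs are excluded, it cites recommended costing methods, and an independent team with its own fuller plan may add these costs. A reader might infer that the program's costs can never enter the analysis. The text does not support that: exclusion is the result of following the stated window and source, not a declared decision. What stands against the reply is that the article is not merely silent. It states a starting point and a source that, applied literally, omit these costs, so a fuller plan that included them would have to depart from this wording.

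Other parts of the reply stand.

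- Not every component falls outside. The nomogram update at admission can be inside the window. LUS visits leave a consultation form and a written consent, and the case report form covers prenatal care, so they may well be charted; only the labour-onset start then drops them.
- The planned breakdown of costs by secondary outcome looks for drivers of change. It does not define total cost and cannot be read as proof that no program-cost category exists.
- The documents do not say who pays for training or the central platform, or which part is research activity. The understatement is therefore not necessarily the full program cost.
- A reader might also infer that the program would wrongly appear both cheaper and better. Without a program cost or a downstream saving in the documents, that cannot be shown.

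**Conclusion.** The concern holds for the rules as stated. They leave most program costs outside the incremental cost, in conflict with the public-payer perspective the section adopts, and the error favours the program. The direction requires only that the payer would bear some of the omitted cost and, for the ICER, that the program reduces morbidity. The multiplier of about $89 per omitted dollar also requires the design effect of 4.5% to 3.375%. The dollar range is illustrative, because no program cost is given. The point is confined to the secondary economic evaluation; the primary clinical analysis, its power and its error control are untouched.

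**What to change.** Amend the *Economic evaluation* section in three ways.

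1. Start the cost window early enough to include the antenatal program components, and apply the same window to both groups and both periods so that other antenatal care is counted alike.
2. Add program delivery costs for women in intervention hospitals during the intervention period: training and recertification spread over eligible women, the LUS visit and scan, central film reading, and time for the decision aid and nomogram. Name program and LUS-clinic records as the source, alongside patient charts.
3. Report the ICER with and without start-up or research-only costs, so that readers can see what would recur in routine use.

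The price is some additional record-keeping, since the article does not say whether such cost records are kept, and a less favourable ICER. Data collection for the clinical outcomes need not change.

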### Potential limitations of the trial

Our study could have some limitations. Since hospitals will be the unit of randomization, and the number of deliveries varies across hospitals, there could be differences in the distribution of hospital characteristics across groups at baseline. These differences will be adjusted a priori in multivariable analyses. Because of potential intra-cluster variation among hospitals, the trial results could be driven by a few hospitals. Consequently, adjusted, center-specific multivariable analyses will be also conducted to assess changes over time in the major perinatal morbidity rates in each individual hospital. Furthermore, the intervention may not be fully implemented in each intervention hospitals. Finally, because we will assess a complex, multifaceted intervention, it will not be possible to determine which of its components will be primarily responsible for any observed effect.

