**Methods/design:**

The study is a stratified, non-blinded, cluster-randomized, parallel-group trial of a multifaceted intervention. Hospitals in Quebec are the units of randomization and women are the units of analysis. As depicted in Figure 1, the study includes a 1-year pre-intervention period (baseline), a 5-month implementation period, and a 2-year intervention period. At the end of the baseline period, 20 hospitals will be allocated to the intervention group and 20 to the control group, using a randomization stratified by level of care. Medical records will be used to collect data before and during the intervention period. Primary outcome is the rate of a composite of major perinatal morbidities measured during the intervention period. Secondary outcomes include major and minor maternal morbidity; minor perinatal morbidity; and TOL and VBAC rate. The effect of the intervention will be assessed using the multivariable generalized-estimating-equations extension of logistic regression. The evaluation will include subgroup analyses for preterm and term birth, and a cost-effectiveness analysis.

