### Inclusion and exclusion criteria

All hospitals entered the trial in April 2016. The study is conducted in 40 out of 48 eligible public hospitals in the province of Québec. To be eligible, each center was required to offer TOL after cesarean in their population; to have a minimum of 300 deliveries in the previous year; to have functional operating rooms; to have access to a high-performance sonographic device; and at the time of recruitment, to have no recent or ongoing quality-improvement programs specifically designed to target women with one prior cesarean delivery. Hospitals where LUS thickness measurement was already available in routine clinical practice and will remain available during the study were excluded from the trial.

At the patient level, women with only one prior cesarean delivering at one of the participating centers at a minimum of 24 weeks with one newborn who weighs at least 500 g at delivery are included in the analyses. Women with delivery or miscarriage before 24 weeks of gestation, with more than one previous cesarean delivery or with multiple gestations will be excluded from the trial.

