### Statistical analysis plan

#### Sample size and power calculation

The sample size was calculated to maximize statistical power while minimizing the number of clusters [64]. Sample size calculations were based on a cluster RCT design [65], stratified by level of care (community, regional or tertiary care hospitals), to detect a relative reduction of 25% in major perinatal morbidity in hospitals of the intervention group compared with those of the control group. To account for clustering by hospital, we assumed an intraclass correlation coefficient of 0.001, estimated from the QUARISMA Trial data, representing 70% of deliveries in Quebec in 2010–2011 [64]. We calculated that we would have to enroll 40 hospitals in the study, with an expected total of 7360 women with one prior cesarean delivery per year (22,080 women for the 1-year baseline period and the 2-year intervention period), to achieve a power of 80% to detect a 25% relative reduction with the intervention in the major perinatal morbidity rate, assuming a baseline rate of 4.5% for the three strata, at a two-sided alpha significance level of 0.05 [64, 66].

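### The hospital-by-hospital before-after analyses do not show whether a few hospitals drive the result; leave-one-hospital-out refits of the primary model would

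*Protocol article*

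**What the plan says.** Under Potential limitations of the trial, the protocol article recognises that, because hospitals differ, "the trial results could be driven by a few hospitals". As the direct consequence it promises that "adjusted, center-specific multivariable analyses will be also conducted to assess changes over time in the major perinatal morbidity rates in each individual hospital". It states no other check aimed at individual hospitals.

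The Statistical analysis section defines the main measure of effect differently. It is the adjusted odds ratio for the interaction of group and period, a difference-in-differences estimated from all hospitals together by GEE logistic regression with an exchangeable correlation.

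The planning figures are under Sample size and power calculation: 40 hospitals, an "expected total of 7360 women with one prior cesarean delivery per year" ("22,080 women for the 1-year baseline period and the 2-year intervention period"), "assuming a baseline rate of 4.5% for the three strata" and a 25% relative reduction. The abstract gives the split: "20 hospitals will be allocated to the intervention group and 20 to the control group". Under Inclusion and exclusion criteria a hospital needed only "to have a minimum of 300 deliveries in the previous year", so small units can be present. The distribution of hospital sizes and the number of adjustment variables are not given.

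**The concern.** The threat and the remedy do not match. Whether a few hospitals drive the result is a question about influence: how far would the pooled interaction odds ratio move if a given hospital were absent? A hospital's own before-after change depends on its effect, the secular trend and chance. It contains no comparison with the other arm and takes no account of the hospital's weight in the pooled estimate.

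The second problem is precision. Major perinatal morbidity is uncommon, and one hospital contributes few events. If the single-hospital changes scatter widely even when every hospital has the same true effect, a table of them can neither reassure nor warn. The trial report could then claim robustness, or point to apparently deviant hospitals, on evidence that supports neither.

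**Working it through.** **1. Plan figures.** 3 × 7360 = 22,080, so the stated total reproduces. The stated 80% power is not an input here. (A two-proportion calculation on the intervention period alone, with equal clusters and design effect 1 + 367 × 0.001 = 1.367, gives about 85%. That is a separate matter.)

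**2. Size of an average hospital.** 7360 / 40 = 184 women per year.
- Baseline events: 184 × 0.045 = 8.3.
- Two intervention years, control hospital: 368 × 0.045 = 16.6; total 24.8.
- Two intervention years, intervention hospital at the planned rate of 0.75 × 0.045 = 0.03375: 368 × 0.03375 = 12.4; total 20.7.

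**3. Precision of one intervention hospital's change, unadjusted.**
- Odds ratio = (0.03375/0.96625) / (0.045/0.955) = 0.741; log = −0.299.
- SE = √[1/(184 × 0.045 × 0.955) + 1/(368 × 0.03375 × 0.96625)] = √(0.1265 + 0.0833) = 0.458.
- 95% CI = exp(−0.299 ± 1.96 × 0.458) = 0.30 to 1.82.
- Two-sided power at 0.05: Φ(0.299/0.458 − 1.96) + Φ(−0.299/0.458 − 1.96) ≈ 0.10.
- Chance that the estimate exceeds 1 although the true reduction is 25%: 1 − Φ(0.654) ≈ 0.26. About a quarter of identical intervention hospitals would appear to get worse.
- A hospital with an assumed 400 women per year has 45 to 54 events, a CI of 0.40 to 1.36 and power of 16%, so size alone does not solve this.

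**4. Before-after change is not influence.** As a simplification, weight hospitals within an arm by number of women (20 × 184 = 3680 per year). Omitting a hospital with share w then moves the pooled log odds ratio by w × (its change − the change in the rest of its arm). Take the same departure of 1.96 × 0.458 = 0.90 in three hospitals (30 and 400 are assumed sizes):

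| Women/year | w | Shift in pooled log OR | Factor on OR |
|---|---|---|---|
| 30 | 0.008 | 0.007 | 1.01 |
| 184 | 0.050 | 0.045 | 1.05 |
| 400 | 0.109 | 0.098 | 1.10 |

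An identical hospital-level result has more than ten times the influence in the largest as in the smallest. The planned analysis does not show this.

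**5. Small hospitals (assumption).** The share of deliveries to women with one prior cesarean is not given. At 300 deliveries and an assumed share of 5%, 10% or 15%, there are 15, 30 or 45 eligible women a year. Expected baseline events are 0.7, 1.35 or 2.0, and the chance of none (0.955^n) is 50%, 25% or 13%. The article does not say that any participating hospital is at this minimum.

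**6. Stability of adjusted single-hospital models (assumption).** Logistic models were simulated with binary covariates (prevalence 5 to 30%, log odds ratio 0.5 each), 300 runs per setting. A fit counted as failed if it did not converge or gave an extreme coefficient or standard error.

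| Women/year | 5 covariates | 10 | 15 |
|---|---|---|---|
| 40 | 88% | 97% | 99% |
| 184 | 20% | 31% | 44% |
| 400 | 3% | 4% | 5% |

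**7. Information left after omitting one hospital.**
- Expected events: 331.2 (baseline) + 331.2 (control, intervention period) + 248.4 (intervention arm) ≈ 911. Omitting an average hospital (about 23 events) leaves about 888.
- Interaction SE, ignoring clustering: √[2/(3680 × 0.045 × 0.955) + 1/(7360 × 0.045 × 0.955) + 1/(7360 × 0.03375 × 0.96625)] = √(0.01265 + 0.00316 + 0.00417) ≈ 0.14, against 0.46 for one hospital's change.

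**The case against.** The strongest reply is that the model is not specified. The article gives no covariate list for these analyses, does not say that they carry the full primary set, and does not exclude one pooled model with hospital-by-period terms, in which about 911 events would estimate the covariate effects. A full analysis plan may set a reduced or penalised model. This stands against any claim about fitting. It does not rescue the check: each hospital's change still rests on that hospital's own events, and it still has no concurrent control.

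Other features bear on hospital differences: randomization stratified by level of care, adjustment for hospital characteristics, and the three-way test of level of care, intervention and time. They are real, but they work on tiers or covariates and do not isolate a hospital. Large hospitals, the likeliest to dominate, also have the most stable models. That is true, yet a stable before-after estimate still does not measure influence.

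A reader might infer more than the article supports:
- **That the models cannot be fitted.** About 8 events is the baseline year's mean only; the change uses all three years. At an assumed 400 women a year nearly all simulated fits succeed.
- **That 40 significance tests will produce spurious outliers.** Forty independent tests at 5% would give 2 expected false positives and an 87% chance of at least one (1 − 0.95^40). But the article announces no hospital-level test, threshold or outlier rule.
- **That the trial's conclusion is at risk.** The primary inference is the pooled GEE interaction, and nothing in it depends on these analyses.

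**Conclusion.** The point holds as a minor one. The mismatch between question and method follows from the article's own definition of the effect and needs no assumption about hospital size or covariates. The imprecision follows from the planning figures for an average hospital: 21 to 25 events, an unadjusted CI of about 0.30 to 1.82 at the planned effect, and power of about 10%. Real differences between hospitals could not be told from chance. Instability of separately fitted adjusted models is likely in small hospitals and possible in average ones, but this depends on a covariate number and a size distribution that the article does not give. What is weakened is the supplementary conclusion about robustness to individual hospitals.

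**What to change.** State leave-one-hospital-out refits of the primary GEE model as the check: omit each of the 40 hospitals in turn, and report the range of interaction odds ratios with their confidence intervals and the hospitals whose omission moves the estimate most. If hospital-specific changes are still shown, present them descriptively, preferably as shrunken estimates from one pooled model with a random hospital-by-period term, in a forest plot without hospital-level significance tests. Fix this before the allocation is revealed to the analysts. The cost is 40 refits of an existing model and a short change of text. No new data are needed, and the primary analysis does not change.
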